### Harms

2.15

This study is of a cognitive-practical nature, and participants may not derive any direct clinical benefit. The proposed OFC procedures at each stage of hen's egg protein tolerance assessment are consistent with standard clinical practice. The only distinction introduced by this study is the random allocation to either an 18-week or 24-week observation arm. Outside the context of the study, the timing between OFCs would be determined solely at the discretion of the child's attending physician.

The assessment of patient and caregiver quality of life, as well as caregiver anxiety levels, requires an additional time commitment of approximately 15 min to complete standardized questionnaires designed to assess these domains.

All adverse events will be systematically documented in the Clinical Research Form (CRF) and categorized based on the International Council on Harmonization Good Clinical Practice (ICH-GCP) guidelines (32). Each event will be thoroughly evaluated to determine its duration, severity, and potential relationship with the administered intervention.

To ensure timely reporting and clinical assessment of any adverse events, participants will have access to the principal investigator via telephone and electronic mail.

In accordance with the CONSORT extension for harms reporting (33), all reported symptoms will be documented for all randomized participants, regardless of whether they complete the study. Adverse event data will be reported separately for each study arm and for each specific type of event, including the exact frequency of occurrence and distinguishing between participants with single and recurrent events.

### Sequence generation and allocation concealment

2.16

Children will be randomised to either the intervention or control group immediately after enrolment. An independent investigator with no clinical involvement in the trial will generate random assignments using a computer-generated random number table. The random number will be generated in blocked randomization (using the block of 2) with a 1:1 allocation ratio. The randomization will be created using StatsDirect statistical software (Stats-Direct statistical software; http://www.statsdirect.com; England: StatsDirect, 2024).

Allocation concealment will be ensured through the use of opaque, sealed and numbered envelopes. The data regarding intervention assignments will be stored in a sealed envelope in a secure location within the administrative part of the department. An independent person will open the next consecutively numbered envelope and provide the allocation information to the study physician.

Since this is an open-label trial, both the participants and the study team will be aware of the treatment allocation on randomization. In the event of any medical issues, the assigned treatment information will already be accessible to the study physicians and principal researcher, eliminating the need for code-breaking procedures.

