### Study objective and hypothesis

2.1

The primary aim of this study is to evaluate and compare the efficacy and safety of a 4-step egg ladder (4-EL) and a 5-step egg ladder (5-EL) in children diagnosed with IgE-mediated hen's egg protein allergy.

We hypothesize that the 4-EL, with 6-week intervals, will be sufficient for assessing tolerance to hen's egg proteins in children with IgE-mediated allergy and will result in a greater proportion of children achieving tolerance to raw egg white, confirmed by OFC, compared to the 5-EL, with the same timeframe. This corresponds to an 18-week tolerance acquisition period in the 4-EL group vs. 24 weeks in the 5-EL group.

There is some evidence suggesting that the introduction of baked egg in high-risk children (e.g., those with a history of anaphylaxis) may be both safe and effective (21). However, it remains unclear whether the initial tested dose of baked hen's egg protein in such cases should be lower than, or the same as, that recommended for the general pediatric HEA population.

Therefore, we decided to compare two ladder protocols: the 4-EL, beginning with a muffin containing 1.5 g of hen's egg proteins, and the 5-EL, in which the first two steps consist of muffins containing 0.75 g and 1.5 g of egg proteins, respectively. This approach allows for a reduced allergen load at initial exposure and a longer cumulative exposure to baked hen's egg proteins. Such a strategy may be more appropriate for specific subgroups of patients, particularly those considered to be at higher risk (21).

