### Study design

2.2

To compare both treatment strategies, we will conduct a multicenter, open-label, randomized superiority trial with two parallel arms and a 1:1 allocation ratio.

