### Study procedure

2.6

Children aged 12 months to 5 years with a confirmed diagnosis of IgE-mediated HEA will be invited to participate in the study. During a medical visit at the department, the recruiting physician will conduct a thorough interview with the parent or guardian, perform a physical examination of the child, review the patient's previous medical records – and perform the eligibility screening.

Children who meet the study eligibility criteria will be randomly assigned to either the intervention or control group. Parents will receive detailed information regarding the study procedure, the upcoming OFC, and the potential benefits and risks of participation. Informed consent will then be obtained from each child's legal guardian, with the form signed in duplicate.

All participating children will begin the introduction of hen's egg proteins into their diet following either the 4-EL (intervention group) or 5-EL (control group). Each subsequent stage of the EL will be initiated with an OFC involving progressively less processed forms of hen's egg proteins: muffin with 0.75 g; muffin with 1.5 g; pancake; hard-boiled egg; soft-boiled egg (Table 2). During the 6-week interval between each stage, parents will introduce the allergen at the previously tolerated dose in the home setting (see Intervention).

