### Blinding

2.17

Due to the nature of the intervention, this study will be unblinded. Participants, caregivers, investigators and outcome assessors will all be aware of treatment allocation.

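### Fixed, published blocks of two in an open-label trial make up to half of the allocations predictable before the child is enrolled

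*Protocol article*

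**What the plan says.** Section 2.16 (Sequence generation and allocation concealment) has an independent investigator without a clinical role produce the list, and fixes the block size: "The random number will be generated in blocked randomization (using the block of 2) with a 1:1 allocation ratio". Section 2.2 likewise specifies "two parallel arms and a 1:1 allocation ratio".

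Section 2.16 then claims concealment: "Allocation concealment will be ensured through the use of opaque, sealed and numbered envelopes". The envelopes are used in order: "An independent person will open the next consecutively numbered envelope and provide the allocation information to the study physician".

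The same section says that "both the participants and the study team will be aware of the treatment allocation on randomization", and section 2.17 (Blinding) adds: "Participants, caregivers, investigators and outcome assessors will all be aware of treatment allocation".

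Under section 2.6, "the recruiting physician will conduct a thorough interview with the parent or guardian", examines the child and screens for eligibility. Section 2.1 says of the 5-EL approach: "Such a strategy may be more appropriate for specific subgroups of patients, particularly those considered to be at higher risk".

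The article mentions neither varied nor withheld block sizes. It does not say whether there is one list or one per department.

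**The concern.** At 1:1, a block of two must hold one 4-EL child and one 5-EL child. The block size is public, the envelopes are consecutive, and each result goes to the study physician. Anyone who has seen the first allocation of a pair knows the second without opening anything. Opaque envelopes hide their contents, but they cannot block this deduction.

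The recruiting physician also has room to act on that knowledge. Table 1 includes criteria that call for judgement (general health, cooperation of the guardians) and criteria that pass with time (acute infection, a flare of another allergic disease, recent antihistamines). Either kind gives an ordinary reason to bring a child forward or defer one. Section 2.1 supplies a possible motive, since it suggests that the 5-EL may suit higher-risk children. If such children were steered to the 5-EL, the comparison of tolerance and of anaphylaxis could shift in favour of the 4-EL, which is the direction of the trial's superiority hypothesis. The primary outcome is an open challenge read by unblinded assessors, so concealment is one of the few protections against bias left in the design.

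**Working it through.** **Inputs.** Block size 2 and ratio 1:1 (sections 2.16 and 2.2). Earlier allocations known to the study team (sections 2.16 and 2.17). Number randomised 94, 47 per arm (section 2.9). Departments: three in section 2.3, two in the abstract.

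**The plan's own number.** 84 completers with 10% dropout: 84 / 0.90 = 93.3, rounded up to 94. Per arm: 42 / 0.90 = 46.7, rounded up to 47. Both reproduce. The article gives no predictability figure.

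**Blocks of 2, whole sequence visible** (a list per department, or recruiters who share allocations).
- The first child of a pair has a guess probability of 1/2. The second is certain.
- Share certain = 1/2, and 94 × 0.50 = 47 children.
- Best-guess success = (0.5 + 1) / 2 = 75%, and 94 × 0.75 = 70.5. Simple randomisation gives 50%.
- The abstract puts the number allocated at 84. The percentages do not change; the certain count would be 42.

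**Blocks of 2, one list shared over sites.** The recruiter sees only their own site's allocations but knows the envelope number. A second-of-pair child is then certain only if the first came from the same site. With site shares w, and each child's site independent of the previous one:
- Share certain = ½ × Σw². Best-guess success = ½ + ¼ × Σw².
- Two equal sites: Σw² = 1/2, so 25% certain (23.5 of 94) and 62.5% guessed.
- Three equal sites: Σw² = 1/3, so 16.7% certain (about 16 of 94) and 58.3% guessed.
- The equal split is an assumption. Σw² is smallest when the shares are equal, so any other split raises these figures.

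**Alternatives, whole sequence visible.** Fixed sizes come from full enumeration of the balanced blocks. The mixed case comes from simulation of 4,000 sequences of 94, with a guesser who knows the set of sizes but not their order.

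| Blocks | Certain | Best guess correct |
|---|---|---|
| Fixed 2 (plan) | 50% | 75% |
| Fixed 4 | 33.3% | 70.8% |
| Fixed 6 | 25.0% | 68.3% |
| Random mix of 4 and 6 | 5.6% (about 5 of 94) | 69.2% |

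Fixed 4 by hand: the fourth child is always certain, and the third is certain when the first two match (probability 1/3), so (1 + 1/3) / 4 = 33.3%.

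**The case against.** The strongest reply is that concealment is partial, not absent. The list-maker and the envelope-opener are independent, and the first child of every pair stays concealed. A reader might infer from blocks of two that nothing is concealed; the text does not support that. This objection stands, and the point is confined to the second child of a pair.

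The 50% figure is also conditional. The article does not say whether lists are per department or shared, so a range is needed. The lower end of 17–25% itself requires that the recruiter knows the envelope number. Without that the certain share would be smaller still. This stands too.

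A reader might further infer that the list is unstratified, that high-risk status is the main prognostic factor, or that no analysis could repair the damage. None of these is supported. The first rests on silence in a condensed article. No section states the second. As to the third, adjustment could address imbalance in a measured baseline factor; only selection on unmeasured factors would escape it.

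Finally, section 2.9 calls this a pilot, and its random error is large. With 47 per arm and tolerance assumed at 69% (the pooled figure in the Introduction), the 95% half-width for the difference is 1.96 × √(2 × 0.69 × 0.31 / 47), or about 19 points. That does not excuse an avoidable source of systematic error, because the effect estimates are meant to inform later trials.

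**Conclusion.** The point holds in limited form. Section 2.16's assurance of concealment fails for up to 50% of allocations (47 of 94, best-guess success 75%) if lists are per department or recruiters share allocations. It fails for about 17–25% under one list shared over three or two equal sites, with own-site knowledge and known envelope numbers. The block size and the open allocation are stated outright, so a fuller protocol or an analysis plan would not remove the problem.

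Selective enrolment is possible, not demonstrated. The documents give neither the share of high-risk children nor tolerance by risk group, so the resulting bias cannot be sized from them.

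**What to change.** Have the independent investigator replace the unused part of the list with randomly varied permuted blocks, for example of 4 and 6, with the new sizes and their order withheld from recruiters. The published block size cannot be withdrawn, only superseded. The registry update foreseen in section 2.20 can say that block sizes vary without giving them.

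Release each allocation only after consent and enrolment. Section 2.6 describes assignment before consent, while section 2.16 places randomisation after enrolment; the two should be reconciled.

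**Gain:** certain guesses fall to about 5–6%. Best-guess success falls only from 75% to about 69%, so the benefit lies mainly in removing certainty.

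**Cost:** one new list and new envelopes. A block of 6 cut short can leave a final imbalance of up to three children per list.

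**Optional:** separate lists per centre. The imbalance limit then applies to each list, so three lists could in the worst case add up to 3 × 3 = 9. Stratifying by high-risk status is not part of this point.

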### Blinding

2.17

Due to the nature of the intervention, this study will be unblinded. Participants, caregivers, investigators and outcome assessors will all be aware of treatment allocation.

### Data collection and management

2.18

All study participants will be assigned a unique study identification number. CRFs will be completed on paper forms. Data will then be entered and stored in a password-protected electronic database. The original paper copies of CRFs and all study data will be stored in a locker within the study site, accessible to the involved researchers only.

### Statistical analysis

2.19

Descriptive statistics will be used to summarize baseline characteristics. For continuous variables, comparisons between groups will be made using the Student's *t*-test, Mann–Whitney *U*-test or Wilcoxon signed rank test, depending on whether or not the variables are normally distributed. The appropriate statistical test will be employed to compare percentages, either the χ^2^ test or Fisher's exact test.

For continuous outcomes, the differences in means or medians (depending on the distribution of data), and for dichotomous outcomes, the relative risk (RR) and number needed to treat (NNT), all accompanied by a 95% CI, will be calculated. The difference between study groups will be considered statistically significant if the *p*-value is less than 0.05, if the 95% CI for RR does not include 1.0, or if the 95% CI for mean difference does not include 0. All statistical tests will be two-tailed and performed at the 5% level of significance.

An intention-to-treat (ITT) analysis including all randomised participants, regardless of protocol adherence or withdrawal, will be applied. A per-protocol analysis that includes all participants who finish the study according to the protocol will also be performed.

The number of missing data with reasons will be reported for each study arm, and compared qualitatively between groups, if feasible. Multiple imputation methods for missing data will be applied to address missing data, as recommended (34).

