#### Laboratory analysis

2.6.3

In all participants, blood samples will be collected prior to each oral food challenge to measure total IgE (tIgE) and specific IgE (sIgE) antibodies to hen's egg white and ovomucoid (Gal d 1). Previous studies have demonstrated the value of assessing the sIgE/tIgE ratio as a predictor of OFC outcomes (28, 29).

In addition, a basophil activation test (BAT) will be performed prior to each OFC. As a functional assay, BAT has demonstrated greater accuracy than sIgE measurement alone in identifying baked and lightly cooked egg allergy. Krawiec et al. (29) found that BAT improves the predictive value for a positive OFC outcome with baked egg and reduces the number of OFCs in children aged 6 months to 15 years with suspected egg allergy.

Both sIgE/tIgE ratio and BAT may support the identification of children who are more likely to tolerate food allergens during OFC. However, its role in predicting response to OFC with baked egg remains to be fully established.

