#### Primary outcome

2.11.1

The primary outcome is the percentage of children who acquire tolerance to soft-boiled hen's egg (almost raw hen's egg proteins), as determined by a negative OFC at the final step of the EL. Soft-boiled egg will be administered at the end of the observation period (18 or 24 weeks, depending on the assigned study arm).

The challenge dose will consist of 0.5–1 egg for children aged 1–3 years and 1 egg for those aged 4–5 years, corresponding to a maximum total of 6 g of hen's egg proteins. The outcome will be reported as a difference between two study arms.

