○grade 1: includes nausea and/or mild abdominal pain without altered activity;○grade 2: persisting (≥20 min) and non-distractable abdominal pain and/or vomiting (not due to gag or taste aversion) and/or diarrhea;○grade 3: severe, persistent (≥20 min), intractable abdominal pain and/or vomiting (excluding retching or taste aversion) and/or diarrhea, assessed during each OFC measured during the observation period (18 or 24 weeks, depending on the study arm).In the subgroup of children with AD, changes in the total score of the oSCORAD index (26) will be assessed before and after each OFC. Any documented exacerbation of AD symptoms following OFC will be also recorded.Change in age-adjusted *z*-scores for weight and length/height, evaluated using the WHO growth charts (31), from baseline (prior to the first OFC) to the end of the observation period (18 or 24 weeks, depending on the study arm).Change in the total score of the FAQLQ-PF (24), at the end of the observation period (18 weeks and 24 weeks, depending on the study arm) from baseline.Mean difference in caregiver anxiety levels, measured by the Subjective Units of Distress Scale (SUDS) (25) prior to each OFC, between study groups at each time point.The proportion of children with full adherence to the intervention protocol, defined as consumption of at least one portion of a tolerated hen's egg proteins dose three times during last week of break in period, in the same form and quantity as tested during the OFC. Data will be collected through the Egg Ladder Monitoring Diary and assessed throughout each break in period (between the following steps of each ladder).

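### Section 2.19 offers a paired rank test for comparing two independent arms; it should go, the change outcomes are better analysed by ANCOVA, and the primary result needs a risk difference

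*Protocol article*

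**What the plan says.** The design is a multicentre, "open-label, randomized superiority trial with two parallel arms and a 1:1 allocation ratio" (section 2.2). Section 2.16 describes randomisation in blocks of 2 and names no matching and no stratification factor.

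Section 2.19 opens its list of tests with "For continuous variables, comparisons between groups will be made using the Student's" t-test, then adds the Mann-Whitney test "or Wilcoxon signed rank test, depending on whether or not the variables are normally distributed". Normality is the only criterion given for choosing among the three.

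For effect measures, section 2.19 gives differences in means or medians for continuous outcomes and, "for dichotomous outcomes, the relative risk (RR) and number needed to treat (NNT), all accompanied by a 95% CI, will be calculated". The risk difference is not named. Section 2.11.1 says of the primary outcome: "The outcome will be reported as a difference between two study arms". Section 2.11.2 says the same of all secondary outcomes.

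Section 2.11.2 defines several continuous outcomes as changes. Growth z-scores are taken "from baseline (prior to the first OFC) to the end of the observation period", the FAQLQ-PF total score is a change from baseline, and oSCORAD (atopic dermatitis subgroup) is a change from before to after each challenge. Caregiver anxiety (SUDS) is compared between arms at each time point.

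**The concern.** The signed rank test ranks within-pair differences. Children in the two arms are not paired, so there are no such differences to rank. Normality cannot separate paired from independent data, so the stated rule gives no ground for choosing between the two rank tests. An analyst who follows the sentence literally could run a test that either fails or gives an arbitrary p-value.

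Two lesser matters sit in the same section. The change outcomes are assigned plain two-sample tests although the baseline value is available as a covariate. And the announced difference for the primary outcome has no matching effect measure in the analysis section. Section 2.9 says that the trial is to supply effect sizes for later confirmatory studies, so the scale and the interval of the primary estimate matter.

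**Working it through.** **Sample size.** From section 2.9: 84 completers, 42 per arm, 10% dropout. 84/0.9 = 93.3, rounded up to 94; 42/0.9 = 46.7, rounded up to 47. The stated 94 (47 per group) reproduces. No power figure is stated. The checks below use 42 per arm.

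**1. Signed rank test on independent arms.**
- *Unequal arms.* The test needs one partner per child, so 41 against 43 cannot be computed. Equal numbers would be chance: section 2.9 expects dropout, and section 2.5.3 takes every child with a positive challenge out of further participation, which thins the later SUDS time points.
- *Equal arms, arbitrary pairing.* Simulation with 6,000 data sets per scenario, 42 per arm; distributions and shifts are assumed.

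| Data | Shift | Signed rank, p < 0.05 | Mann-Whitney, p < 0.05 | Different decisions |
|---|---|---|---|---|
| Normal | 0 | 4.8% | 4.8% | 2.5% |
| Lognormal | 0 (log scale) | 4.6% | 4.4% | 3.4% |
| Normal | 0.6 | 74.5% | 75.0% | 7.4% |
| Lognormal | 0.6 (log scale) | 69.5% | 75.1% | 11.7% |

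- *Row order.* In one simulated lognormal data set (Mann-Whitney p = 0.011), one arm was re-ordered 5,000 times. The central 95% of signed rank p-values ran from 0.007 to 0.10, with 68% of orders below 0.05.

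Type I error therefore stays near nominal. The harm is an arbitrary result and, for skewed data, some loss of power.

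**2. Change score against ANCOVA.** Let r be the correlation of baseline with final value, with equal variances. Relative to the final value alone, the variance of the arm contrast is 2(1-r) for change and 1-r² for ANCOVA. The ratio is (1-r²)/[2(1-r)] = (1+r)/2. The article gives no r, so a range is shown. Power is for 42 per arm and an assumed difference of 0.5 SD of the final score.

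| r (assumed) | Change, 2(1-r) | ANCOVA, 1-r² | Ratio | Power, change | Power, ANCOVA |
|---|---|---|---|---|---|
| 0.3 | 1.40 | 0.91 | 0.65 | 49% | 67% |
| 0.5 | 1.00 | 0.75 | 0.75 | 63% | 75% |
| 0.7 | 0.60 | 0.51 | 0.85 | 84% | 89% |
| 0.8 | 0.40 | 0.36 | 0.90 | 95% | 97% |

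The saving falls from 35% of the variance at r = 0.3 to 10% at r = 0.8, and to 5% at r = 0.9.

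**3. Scale of the primary result.** Illustration: 80% against 69%, the raw-egg tolerance rates of the one egg-ladder RCT cited in the Introduction. These are not planning values of this trial.
- Risk difference: 0.80 - 0.69 = 0.110. SE = √[(0.80×0.20 + 0.69×0.31)/42] = √(0.3739/42) = 0.0944. Half-width 1.96 × 0.0944 = 0.185. 95% CI -7.5 to 29.5 points.
- With 69% in both arms: half-width 1.96 × √(2×0.69×0.31/42) = 0.198.
- RR: 0.80/0.69 = 1.16. SE of log RR = √[0.20/(42×0.80) + 0.31/(42×0.69)] = 0.129. 95% CI 0.90 to 1.49.
- NNT: 1/0.110 = 9.1. The inverted limits are 1/0.295 = 3.4 (benefit) and 1/0.075 = 13.3 (harm). The set runs from 3.4 up to infinity and back from infinity to 13.3 on the harm side, so it is not one continuous range.

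At these rates, an observed difference below about 18 to 20 points leaves the NNT without a usable interval.

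**The case against.** The best defence of the signed rank test is that it was meant for change within an arm and slipped into the wrong sentence, with the correct Mann-Whitney test beside it. That may be the intention, but the sentence concerns comparison between groups, section 2.11.2 reports every secondary outcome between arms, and no within-arm outcome is listed. The stated rule is wrong as it stands. It is fair, though, that type I error is hardly affected and that the primary outcome, tested by chi-squared or Fisher's exact test, is untouched.

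On ANCOVA, the objection is that an unadjusted test of change is valid in a randomised trial and that adjustment is often left to the SAP, which is not shown. Both stand, so this is a recommendation of a better method and not an error. The gain is small where r is high, which may apply to growth z-scores over 18 to 24 weeks, and the figure of 42 per arm does not apply to oSCORAD, which is measured in a subgroup.

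On the primary outcome, the word difference may be used loosely to mean a comparison, and NNT is the reciprocal of the risk difference. This also has force: it is a reporting inconsistency, RR with its CI is always interpretable, and choosing RR costs no precision.

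A reader might go further and infer that baseline values are ignored. They are not, because the change outcomes use them. Nor does the article support saying that the primary comparison must be adjusted for known predictors. It nowhere calls age predictive of challenge outcome. Section 2.6.3 speaks of the sIgE/tIgE ratio and the basophil test, and says that the predictive role for baked egg is not fully established.

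**Conclusion.** The listing of the signed rank test for between-arm comparison is an error in the stated text, confined to continuous secondary outcomes. It makes the test impossible with unequal arms and its result arbitrary with equal ones. The simulated figures rest on assumed distributions and shifts; the dependence on row order does not.

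ANCOVA would improve the change outcomes at almost no cost, with a variance ratio of 0.65 to 0.90 for assumed r of 0.3 to 0.8. The missing risk difference is a mismatch between sections 2.11.1 and 2.19. It matters because the NNT interval breaks down whenever the risk-difference CI includes 0, and that CI has a half-width of about 18 to 20 points at the illustrative rates. Nothing here invalidates the primary test.

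**What to change.** In section 2.19:
- Remove the signed rank test from the between-group list, or limit it explicitly to change within an arm. Use Mann-Whitney for non-normal data between arms.
- Analyse FAQLQ-PF, growth z-scores and, in the atopic dermatitis subgroup, oSCORAD by ANCOVA with the baseline value as covariate, stating for oSCORAD which measurement is the baseline.
- For the primary outcome, name the risk difference with 95% CI as the reported measure and keep RR as supportive. Give no NNT interval when the risk-difference CI includes 0.

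The cost is a few sentences in the protocol or SAP and a little analysis work. No further data are needed, since the baseline values are already collected.

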**Discussion:**

This rigorously designed RCT will provide evidence on the efficacy and safety of the 4-EL in children with IgE-mediated HEA. The findings will inform guideline development groups and further confirmatory trials.

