This rigorously designed RCT will help to compare the efficacy of two ladders: the 4-EL which begins with a higher amount of baked hen's egg proteins (1.5 g), and the 5-EL, in which gradual reintroduction starts with two steps – muffins containing 0.75 g and 1.5 g of egg proteins, respectively. Currently, it is unclear whether the initial reintroduced dose of baked hen's egg protein in children with IgE-mediated HEA, especially those in high-risk groups, should differ from that used in children with mild and moderate non-IgE mediated HEA. This study will be conducted by a research center experienced in RCTs involving children and food allergy. The study team is supported by [name], who serves as a scientific mentor and provides expert oversight in protocol development and clinical decision-making in complex cases. The findings of this RCT will address current evidence gaps and inform guideline development groups regarding the efficacy and safety of the 4-EL in children with IgE-mediated HEA.

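### Anaphylaxis and systemic reactions are to be summarised only by relative risk and NNT with a significance test, which bound an absolute excess of harm poorly at 42 to 47 children per arm

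*Protocol article*

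**What the plan says.** Section 2.1 puts safety in the main objective: "The primary aim of this study is to evaluate and compare the efficacy and safety" of the two ladders. Section 2.2 describes a "randomized superiority trial with two parallel arms and a 1:1 allocation ratio".

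Section 2.11.2 lists as secondary outcomes the proportion of children with anaphylaxis and the proportion with systemic allergic reactions. It states that all secondary outcomes are reported as a difference between the arms.

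Section 2.19 fixes the analysis. Percentages are compared by chi-square or Fisher's exact test. Dichotomous outcomes get RR and NNT, each with a 95% interval. A difference counts as significant if p is below 0.05 or the RR interval excludes 1. "All statistical tests will be two-tailed and performed at the 5% level of significance". No risk difference is named for dichotomous outcomes.

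Section 2.9 plans 94 children (47 per arm) so that 84 (42 per arm) complete. It says there is no formal power calculation and calls the trial a pilot. The Discussion nevertheless expects the findings to "inform guideline development groups regarding the efficacy and safety of the 4-EL in children with IgE-mediated HEA".

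**The concern.** For a harm, the useful question is how large an absolute excess the data leave open. The measures fixed in section 2.19 answer it poorly.

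- **NNT.** It is the reciprocal of the risk difference. When the interval for the difference includes zero, the NNT interval splits into a harm part and a benefit part joined at infinity. That is the case whenever the difference is not significant, a likely result for a harm in a trial of this size.
- **RR.** The usual log-scale interval needs at least one event in each arm. Where it does exist, it is a ratio and shows no absolute excess.
- **Test.** With 42 to 47 children per arm, non-significance is expected over much of the plausible range even if the 4-EL doubles the risk.

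At stake is what the trial can say about anaphylaxis in young children, including high-risk children, whom Table 1 admits. If the report gives a non-significant p-value and an uninterpretable NNT interval, readers cannot see the excess that has not been ruled out.

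**Working it through.** **The plan's own figure.** Recruitment is 84 / (1 − 0.10) = 93.3, rounded up to 94, or 42 / 0.9 = 46.7, rounded up to 47 per arm. This agrees with section 2.9. No power figure is stated, so there is none to reproduce.

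**Inputs.** 47 randomised and 42 completing per arm (section 2.9); two-sided 5% and chi-square or Fisher (section 2.19). The protocol gives no anaphylaxis rate, so the 5-EL rate p is an assumption, varied from 3% to 30%, with 2p on the 4-EL.

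**1. Chance that a true doubling is not significant.** All 2×2 tables were enumerated with independent binomial probabilities. Rule: Fisher if the smallest expected count is below 5, otherwise uncorrected chi-square; significant if p < 0.05. Also counting tables whose RR interval excludes 1 does not change the rounded figures.

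| 5-EL vs 4-EL | 47 per arm | 42 per arm |
|---|---|---|
| 3% vs 6% | 98% | 99% |
| 5% vs 10% | 92% | 94% |
| 10% vs 20% | 72% | 76% |
| 15% vs 30% | 58% | 61% |
| 20% vs 40% | 43% | 48% |
| 30% vs 60% | 16% | 17% |

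**2. Chance that at least one arm has no event.** P = 1 − [1 − (1 − p)^n] × [1 − (1 − 2p)^n], with n = 47.

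- 3% vs 6%: 1 − (1 − 0.239)(1 − 0.055) = 28%.
- 5% vs 10%: 1 − (1 − 0.090)(1 − 0.007) = 10%.
- 10% vs 20%: 0.7%.

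**3. What each measure shows for an observed doubling, 6 vs 3 of 47.**

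- Fisher p = 0.49.
- RR = 2.0. Standard error of log RR = √(1/6 − 1/47 + 1/3 − 1/47) = 0.676, so the 95% interval is 0.53 to 7.5.
- Risk difference = 3/47 = 6.4 points. The Wilson limits are 0.060 to 0.252 for 6/47 and 0.022 to 0.172 for 3/47. Newcombe upper limit = 0.064 + √[(0.252 − 0.128)² + (0.064 − 0.022)²] = 0.195. Lower limit = 0.064 − √[(0.128 − 0.060)² + (0.172 − 0.064)²] = −0.064.
- NNT = 1/0.064 = 15.7 to harm. Its interval runs from 1/0.195 = 5.1 to harm, through infinity, to 1/0.064 = 15.7 to benefit.

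The risk-difference interval says directly that an excess of up to 19.5 points is not excluded.

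**4. Equal counts.** The Newcombe upper limit at 47 per arm is 13.4 points for 5 vs 5 and 10.5 points for 2 vs 2. The corresponding RR upper limits are 3.2 and 6.8.

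**5. Zero events.** For 3 vs 0 of 47 the usual RR interval does not exist. The Newcombe interval for the difference is −2.3 to 17.2 points.

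**The case against.** A fair defence has several parts.

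- **The trial is a declared pilot.** Sections 2.9 and 3 admit the missing power calculation and say the trial will supply effect estimates for confirmatory work. This stands, and it supports reporting safety as estimation.
- **An upper limit is already planned.** Section 2.19 gives a 95% interval for RR, which has one. This also stands: it would be wrong to say that no bound is planned. The gap is an absolute bound that still exists with zero events.
- **Zero-event arms are not common.** At 47 per arm the chance is under 1% at 10% vs 20%; it matters only at low rates. With no events on the 4-EL alone, RR is still 0 and other interval methods exist. The NNT problem does not depend on zero events.
- **Harm could run either way.** The 5-EL has one more challenge and six more weeks of exposure. A two-sided interval covers both directions.
- **Interval methods belong in an analysis plan.** The choice between Newcombe and Miettinen-Nurminen could be left there. But the article itself fixes RR and NNT, and these do not match the difference promised in section 2.11.2.
- **Other safeguards exist.** Adverse events are reported by arm for all randomised children (section 2.15), and a monitoring board reviews them (section 2.20). These do not quantify the excess left open.

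A reader might infer something stronger from "We hypothesize that the 4-EL, with 6-week intervals, will be sufficient for assessing tolerance to hen's egg proteins in children with IgE-mediated allergy": that the trial means to show the 4-EL is not worse, has no margin for doing so, and can rely only on a null result. The text does not support that. Section 2.5.2 uses similar wording about the 6-week interval, which both arms share. The comparative hypothesis is that the 4-EL "will result in a greater proportion of children achieving tolerance to raw egg white, confirmed by OFC, compared to the 5-EL", and significant superiority would also support sufficiency. Nowhere does the protocol say that non-significance will be read as safe or sufficient.

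**Conclusion.** The point holds as a limited one about effect measures and interpretation. Section 2.19 gives dichotomous harms only RR, NNT and a significance rule, while section 2.1 makes safety part of the primary aim and section 2.11.2 promises a difference. RR and NNT do not give a usable absolute bound when the difference is non-significant or an arm has no event.

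The size depends on an anaphylaxis rate that the protocol does not give. A true doubling would be non-significant in 58% to 94% of trials for 5-EL rates of 5% to 15%, in 98% to 99% at 3%, and in 16% to 17% at 30%, across 47 and 42 per arm. Except at high event rates, non-significance would say little about safety.

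It does not follow that the superiority design is wrong, that a margin had to be set, or that the investigators intend to claim safety from a null result.

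**What to change.** In section 2.19 add, in substance: for anaphylaxis and each systemic-reaction outcome, the risk difference (4-EL minus 5-EL) will be reported with a two-sided 95% Newcombe or Miettinen-Nurminen interval, in place of or beside NNT. Its upper limit will be stated as the largest excess risk on the 4-EL that the trial does not exclude. In line with the pilot status in section 2.9, the safety comparison will be presented as estimation, and equal safety will not be concluded from a non-significant test.

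This also brings section 2.19 into line with the difference promised in section 2.11.2.

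The cost is a few sentences and one interval per outcome, with no added children, visits or procedures. The downside is that the safety comparison will probably be reported as inconclusive.
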